### Dissemination of results

Following the receipt and analysis of the food diary and the completion of the biochemical assays at screening, each participant will receive a feedback form. Anthropometric measurements and blood results (iron studies, vitamin B_12_, folate and full blood count) will also be included. Once recruitment into the trial is completed, participants who have not proceeded into the trial will receive notification of their vitamin D and RBC fatty acid levels.

On completion of the trial, participants will be informed of their baseline and end vitamin D and RBC fatty acid status, and whether they were taking the active or placebo dose. They will also receive a summary of psychological assessment outcomes of SRS-2 and SPM.

Participants and other stakeholders (such as health professionals, district health boards, primary health organisations, ASD support groups) will be given access to the study’s findings. Results will be presented at scientific conferences both nationally and internationally, prepared for publication in peer-reviewed journals, and circulated to the media.

### Data handling and statistical analysis

Name and address details will be maintained in Microsoft Excel. Check boxes will record the progress of a participant through the study. All other data will be entered into a single Microsoft Excel spreadsheet with participants identified only by their unique Subject Number. Scorings of the questionnaires will be double-checked by the psychologist and the researcher. All entries will be double-checked by another member of the research team. All documents will be stored safely under confidential conditions and archived for 5 years.

Statistical analysis will be performed using IBM SPSS version 21.0 (IBM Corp; released 2012. IBM SPSS Statistics for Windows Version 21.0. Armonk, NY, USA). Before commencement of statistical analysis the data will be cleaned and checked for coding errors. The data will be checked for plausibility by randomly checking the accuracy and completeness and verifying against source data. The variables will be tested for normality using the Kolmogorov-Smirnov test, the Shapiro-Wilk test and normality plots. Non-normally distributed data will be transformed into approximate normal distributions by logarithmic transformations. The data will be reported appropriately as mean (standard deviation) for normally distributed data; transformed data will be back-transformed from summary statistics into geometric mean (95 % CI), non-normally distributed data will be described as median (25th, 75th percentiles) and categorical data as frequencies.

Baseline characteristics of participants will be compared among groups using analysis of variance (ANOVA) for parametric data and the Kruskal-Wallis test for non-parametric data. The primary analysis, comparing the effects of treatment on symptoms of autism over 12 months, will be conducted using a generalised linear mixed-models procedure. Treatments and time will be included as fixed effects and the interactions between interventions and time will be tested. If significant main effects or interaction effects are observed, post-hoc analysis with Bonferroni adjustments will be performed. Potential confounding factors and effect modifiers (e.g. baseline 25(OH)D and RBC fatty acids, symptoms of autism at baseline, age and gender) will be investigated within the model. Logistic regression will be used to test the multiplicative interaction. Rothman’s synergy index, which would be equal to unity under additivity, and less than unity when suggesting antagonism, will be utilised to examine the postulated interaction effect of vitamin D and omega-3 LCPUFAs on core symptoms of ASD.

The secondary analysis, comparing the effects of treatment on gastrointestinal symptoms over 12 months, will be conducted using the same procedure. Potential confounding factors and effect modifiers (e.g. baseline diagnosis of any gastrointestinal symptoms and medication/supplement use) will be investigated within the model.

Differences between participants who complete and withdraw from the trial will be analysed using an independent *t* test or the Mann–Whitney test for continuous variables (e.g. age) and chi-square for categorical variables (e.g. gender).

Associations between severity of ASD symptoms and nutritional status (specifically, vitamin D, RBC fatty acids, iron and vitamin B_12_) at baseline will be assessed using regression analysis. The information will be used to assess treatment response according to tertiles of nutritional status showing significant relationship with severity of ASD.

Both intention-to-treat and per-protocol analyses will be utilised, though the primary method of analysis will be intention-to-treat. Statistical significance will be based on two-tailed tests with *P* <0.05 considered significant.

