**Methods/design:**

Children with ASD living in New Zealand (*n* = 168 children) will be randomised to one of four treatments daily: vitamin D (2000 IU), n-3 LCPUFAs (722 mg DHA), vitamin D (2000 IU) + n-3 LCPUFAs (722 mg DHA) or placebo for 12 months. All researchers, participants and their caregivers will be blinded until the data analysis is completed, and randomisation of the active/placebo capsules and allocation will be fully concealed from all mentioned parties. The primary outcome measures are the change in social-communicative functioning, sensory processing issues and problem behaviours between baseline and 12 months. A secondary outcome measure is the effect on gastrointestinal symptoms. Baseline data will be used to assess and correct basic nutritional deficiencies prior to treatment allocation. For safety measures, serum 25-hydroxyvitamin D 25(OH)D and calcium will be monitored at baseline, 6 and 12 months, and weekly compliance and gastrointestinal symptom diaries will be completed by caregivers throughout the study period.

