Reports on the benefits of n-3 LCPUFAs in treating ASD are inconclusive. There are, to our knowledge, only four randomised, placebo-controlled trials [38–41], three of which are small pilot studies. Bent et al. [40] and Amminger et al. [39] found that omega-3 supplementation was superior over a placebo (12 and 6 weeks, respectively) for reducing symptoms of hyperactivity and stereotypic behaviour in children with ASD. However, more recent studies have found that supplementation with n-3 LCPUFAs for 6 months had no beneficial effect on core symptom domains of ASD in children aged 2 to 5 years (*n* = 38) [41] and 3 to 10 years (*n* = 48) [38]. However, these studies are limited by their low participant numbers and short treatment periods.

In addition to these studies on the nutrients’ effects when given individually, there are speculations that vitamin D and n-3 LCPUFAs may improve ASD symptoms because of their shared functions and each nutrient-specific role that complements the other nutrient’s functions [42, 43]. Both nutrients are powerful anti-inflammatory agents, immune modulators and neuroprotectors [42]. Furthermore, evidence suggests that while vitamin D regulates serotonin synthesis, omega-3 fatty acids increase serotonin release and membrane fluidity and thus increase serotonin accessibility [43]. ASD is associated with increased inflammation, oxidative stress, immune dysregulation and/or mitochondrial dysfunction in brain regions that are involved in social behaviour, sensory and motor coordination, memory, speech and auditory processing, and also with neurotransmitter dysregulation [17, 18, 44].

Gastrointestinal problems have also been reported to be common in children with ASD. Compared to their typically developing siblings (12 %), autistic children have more gastrointestinal symptoms (42 %) [3–5]. Gastrointestinal problems may relate to abnormal gut flora [45], decreased activity of digestive enzymes [46] or increased intestinal permeability [47]. Vitamin D deficiency has been implicated in the pathophysiology of some gastrointestinal diseases, including inflammatory bowel disease [48], and thus might play a role in ASD-related gastrointestinal problems. Likewise, n-3 LCPUFAs have been shown to reduce symptoms of ulcerative colitis [49], to support epithelial integrity in vitro [50], and to alter the gut microbiota composition of both neurodevelopmentally normal and early life-stressed animals [51].

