*Gastrointestinal symptoms questionnaire*: the gastrointestinal symptoms questionnaire is designed specifically for this study and includes gastrointestinal signs and symptoms most commonly reported in children with ASD [81, 82]. Caregivers of study participants will be provided with weekly online diaries and will be asked to record if the child had constipation, diarrhoea, flatulence, abdominal pain, vomiting/nausea, abdominal distension, unexplained daytime irritability or/and unexplained night-time awakening during the past week, and if so how many times these occurred. The gastrointestinal symptoms questionnaire has not been validated, but includes questions on gastrointestinal symptoms most widely reported in ASD populations, or behaviours that might be a consequence of gastrointestinal symptoms. We are not aware of a validated instrument for assessing gastrointestinal symptoms in autistic children, and certainly not in New Zealand.

*Dietary Index of Children’s Eating (DICE)*: the DICE is a simple diet-quality assessment tool which has been developed by the research team, based on the New Zealand Ministry of Health Food and Nutrition Guidelines for Healthy Children and Young People [83]. This tool has been validated in a cohort of New Zealand healthy children aged 2 to 8 years (unpublished), and will be validated in ASD children in this study against the 4-day estimated food diary and biochemical markers.

*Behavioural Paediatrics Feeding Assessment Scale (BPFAS)*: the BPFAS is a simple assessment tool which measures a child’s mealtime behaviour and parents’ attitudes and behaviours. It is a 35-item scale questionnaire comprising 25-likert scale (5 points) questions about child behaviour and 10 dichotomous questions about parents’ attitudes and behaviours. Cut-off scores for the BPFAS have recently been established [84]. The BPFAS is the most reliable parent-administered feeding questionnaire, with good internal validity and test-retest reliability [85].

*Four-day estimated food diary*: dietary intake data will be collected by a 4-day estimated food diary, including one weekend day. Instructions on how to accurately complete the food diary will be provided with the food diary. Participants will be given a free-post, pre-addressed envelope for the return of the booklet. Average macro and micronutrient intake will be assessed over four reported days using FoodWorks Professional Edition 7 (Xryis Software, Brisbane, QLD, Australia, 2012).

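### The blanket log-transformation rule cannot be applied to the gastrointestinal counts, which contain zeros, and it would put the SRS-2 effect on a scale other than the one planned

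*Protocol article*

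**What the plan says.** The article's section on data handling and statistical analysis sets a two-step rule. First, "The variables will be tested for normality using the Kolmogorov-Smirnov test, the Shapiro-Wilk test and normality plots". Then, "Non-normally distributed data will be transformed into approximate normal distributions by logarithmic transformations". The rule has no exception for outcomes and no restriction to positive variables, and it names no added constant. For reporting, the same paragraph says that transformed data will be "back-transformed from summary statistics into geometric mean (95 % CI), non-normally distributed data will be described as median (25th, 75th percentiles".

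The secondary outcome is described under Questionnaires. In weekly online diaries caregivers record whether each of eight symptoms or behaviours occurred "during the past week, and if so how many times these occurred". The analysis "comparing the effects of treatment on gastrointestinal symptoms over 12 months, will be conducted using the same procedure" as the primary one, that is, a generalised linear mixed model with treatment, time and their interaction. No distribution or link is named. Intention-to-treat is the primary method of analysis.

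For the primary outcomes, the abstract says: "The primary outcome measures are the change in social-communicative functioning, sensory processing issues and problem behaviours between baseline and 12 months". The sample size rests on a 17-unit difference in the change in SRS total score.

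**The concern.** A logarithm exists only for values above zero. The diary asks for a number of occurrences only if a symptom was present, so a symptom-free record is zero by construction. An analyst who follows the rule has two ways out. One is to let the zeros become missing. The lost records are then those without symptoms, so the loss depends on the outcome and, if a supplement works, on the arm. The other is to add a constant before taking logs, and the article does not fix that constant.

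The trigger is also misplaced. What matters for a linear model is the distribution of the residuals, not that of the raw variable pooled over arms and visits. A skewed raw variable could send an outcome to the log scale when the model did not need it. For SRS-2 that would replace the unit difference on which the trial was sized with a ratio, on the strength of a test run on the trial data.

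**Working it through.** **The plan's own figure.** The article's formula with SD 24.7, K = 7.9 and a difference of 17 gives 2 × 24.7² × 7.9 / 17² = 33.35, rounded up to 34 per arm. Allowing for 20% dropout, 33.35 / 0.8 = 41.7, so 42. The stated size reproduces, and it is expressed in SRS units.

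**Would the rule be triggered for gastrointestinal counts?** The article gives no share of zeros on its diary. The Background says "autistic children have more gastrointestinal symptoms" than their siblings, at 42%. If, as an assumption, that share applied here, 1 − 0.42 = 0.58 of values would be zero.
- A single value holding 58% of the data makes a jump of 0.58 in the empirical distribution. No continuous normal curve can lie closer to it than half the jump, 0.29.
- The approximate 5% critical value of the Kolmogorov-Smirnov test is 1.36/√n: 1.36/√168 = 0.105 and 1.36/√42 = 0.21. Both are below 0.29.
- At n = 168, any single value holding more than 2 × 0.105 = 21% of the data would trigger the rule. The trigger therefore does not need 58%.

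**What the log analysis would estimate (illustration).** Assume 42% of control values and 21% of treated values are above zero, with the same count distribution among those with symptoms. In the simulation that distribution was log-normal with median 4 and log-SD 0.8, rounded up.
- True ratio of means: 0.21 / 0.42 = 0.50.
- Zeros set to missing: the ratio of geometric means is 1.00. This follows from the assumption, because only the unchanged part is compared.
- Constant added before the log:

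| Constant | Ratio obtained |
|---|---|
| 0.1 | 0.44 |
| 0.5 | 0.61 |
| 1 | 0.69 |

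The same data thus give anything from 0.44 to 1.00, according to a choice that the article leaves open.

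**Does another stated route cover the treatment comparison?**
- The median and quartiles are a way of describing data.
- The Kruskal-Wallis test is assigned to baseline comparisons.
- The Mann–Whitney test is assigned to completers against withdrawals.

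None of these applies to the treatment effect. The mixed model could take a count distribution, but none is named, and a rule that transforms outcomes towards normality suits a normal-errors model.

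**SRS-2 total score.** With mean 105 and SD 24.7, 105 / 24.7 = 4.25, and the normal probability of a value at or below zero is about 0.00001. No child would be lost. On the log scale, however, a 17-unit fall from 105 becomes 88 / 105 = 0.84, a ratio rather than the planned difference.

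**The case against.** The strongest reply is that the article plans no exclusion. Records are lost only if the variable fails the test, the log is forced, no constant is added, the missing values are accepted and no count distribution is used. The paragraph keeps a class of non-normal data described by medians, so it seems to expect some variables to stay untransformed. The named model class can handle counts, and an article may leave the distribution and link to a fuller plan. The researchers are also blinded until the analysis is complete, so a choice of scale could not be steered by treatment.

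Much of this stands. A reader might infer that the children with the best outcomes will drop out; the documents do not say so, and with weekly diaries a lost zero removes a record, not necessarily a child. For the same reason a count of about 14 v 7 children left out of 34 per arm (34 × 0.42 and 34 × 0.21) does not follow. The 42% is a background prevalence, not the share above zero on this diary. That share of zeros could be lower for totals over eight items and many weeks, or higher for single symptoms. The result of 1.00 is an extreme built into its assumptions.

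A reader might also infer that the primary change scores, which can be negative, will be logged. The model has time and treatment-by-time terms, which points to scores at each visit. Nor can zeros in the ABC-C domains be confirmed, since the article gives no score range.

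What the reply does not remove is the stated rule itself. It is written as an instruction without exception, and for a count with a natural zero it cannot be carried out. Blinding prevents steering by arm, but the estimate would still depend on an unstated constant.

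**Conclusion.** The point holds for the gastrointestinal outcome, the trial's only secondary outcome. As written, the rule is either undefined for symptom-free records or depends on a constant that the article does not fix. Dropping those records would conflict with the intention-to-treat analysis. This follows from the diary's definition and needs no outside figure.

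The size cannot be taken from the document. The contrast of 1.00 with 0.50, and the range 0.44 to 0.69 with added constants, rest on three assumptions: 58% zeros in the control arm, a halving of the share with symptoms, and unchanged counts among the rest.

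For the SRS-2 total score the point is minor: no loss of children, but a possible data-driven switch from a difference to a ratio. The documents do not support a claim that primary change scores will be logged, that ABC-C domains will lose children, or that any stated number of children will be excluded. The point deserves correction, at moderate weight for the secondary outcome.

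**What to change.** - Limit log transformation to strictly positive biomarkers.
- Analyse SRS-2 on its original scale, so that the result can be read against the 17-unit difference, and judge normality on model residuals instead of raw variables.
- Analyse gastrointestinal counts in the generalised linear mixed model already planned, with a negative-binomial distribution and log link. The link acts on the expected count, so zero records stay in and no constant is needed.

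The cost is a change of wording, best made before unblinding; the class of model stays the same. The downside is that gastrointestinal effects are reported as rate ratios rather than as differences or ratios of geometric means.

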# Vitamin D and omega-3 fatty acid supplements in children with autism spectrum disorder: a study protocol for a factorial randomised, double-blind, placebo-controlled trial

**DOI:** 10.1186/s13063-016-1428-8

**Published:** 2016-06-23

**Keywords:** Autism, ASD, Vitamin D, Omega-3 fatty acids, Supplements

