## Abstract

**Background:**

There is strong mechanistic evidence to suggest that vitamin D and omega-3 long chain polyunsaturated fatty acids (n-3 LCPUFAs), specifically docosahexaenoic acid (DHA), have the potential to significantly improve the symptoms of autism spectrum disorder (ASD). However, there are no trials that have measured the effect of both vitamin D and n-3 LCPUFA supplementation on autism severity symptoms. The objective of this 2 × 2 factorial trial is to investigate the effect of vitamin D, n-3 LCPUFAs or a combination of both on core symptoms of ASD.

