### Participants

This study is a collaboration between Massey University and the Waitemata District Health Board (WDHB), New Zealand. Caregivers of children who meet the criteria for the study will be approached in the first instance by the WDHB Developmental Coordinators.

We calculated that 42 participants (a minimum of 34 participants, and allowing for a 20-% potential dropout rate) would be required for each arm of the trial to demonstrate a clinically significant difference at 80 % power and 5 % statistical significance. Power calculations were based on a 17-unit difference between supplemented groups and placebo in change from baseline to endpoint on the Social Responsiveness Scale (SRS) total score [62], on a mean SRS and standard deviation of 105 and 24.7 units in untreated children with ASD, respectively (from our 2015 pilot study, unpublished). The sample size was calculated using the formula below [63]:$$ N= 2{\alpha}^2K/{\left({\mu}_2\hbox{-} {\mu}_1\right)}^2 $$

where *N* is the sample size required per group, *α* is the SD, K is the constant (7.9 denotes 80 % power and 5 % significance), and (*μ*_2 −_*μ*_1_) is the difference in SRS total score between groups.

To ensure that the study is adequately powered, a blinded interim analysis at >50 % of the initially planned enrolment will be performed by an independent third party to estimate the variance for potential sample size increase.

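### The 2 × 2 factorial plan does not say how treatment is coded or which contrast decides that a nutrient works, and the candidate contrasts can give different answers

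*Protocol article*

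**What the plan says.** **Design.** The protocol article's title announces "a study protocol for a factorial randomised, double-blind, placebo-controlled trial", and the abstract says "The objective of this 2 × 2 factorial trial is to investigate the effect of vitamin D". Children "will be randomised to one of four treatments daily": vitamin D, n-3 LCPUFA, both, or placebo.

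**Sizing (*Participants*).** "Power calculations were based on a 17-unit difference between supplemented groups and placebo in change from baseline to endpoint", giving "42 participants (a minimum of 34 participants, and allowing for a 20-% potential dropout rate) would be required for each arm".

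**Hypotheses.** The second says that improving either nutrient's status will reduce severity, and names no comparator. The third compares the combination with each supplement alone and with placebo.

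**Primary analysis (*Data handling and statistical analysis*).** A generalised linear mixed model is used: "Treatments and time will be included as fixed effects and the interactions between interventions and time will be tested". Then: "If significant main effects or interaction effects are observed, post-hoc analysis with Bonferroni adjustments will be performed". The post-hoc comparisons are not listed. The only interaction named for this model is with time. The interaction between the two nutrients is assigned to logistic regression and Rothman's synergy index.

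**The concern.** A 2 × 2 factorial supports several answers to the question of whether vitamin D works:

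- the margin: the two arms that contain vitamin D against the two that do not;
- vitamin D alone against placebo;
- the combination against placebo;
- a joint test across all four arms.

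The design label points to the first. The sizing points to a single arm against placebo. The third hypothesis adds comparisons between arms. The model sentence fits one four-level factor or two two-level factors. This matters for the SRS-2 total alone, so it is separate from the question of having three primary scales.

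Two things are at stake. The same data could show a nutrient effective on one contrast and not on another, with nothing in the analysis section to say which one counts. Also, the interaction that the sponsor postulates would be examined by methods for a binary outcome. That means cutting continuous scores into two groups, when the mixed model could carry the term directly.

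**Working it through.** **Inputs.** From *Participants*: difference 17 SRS units, SD 24.7, K = 7.9 (80 % power, 5 % significance), 34 completers and 42 randomised per arm. From the analysis section: two-tailed tests at 0.05. Assumed: equal allocation, 24.7 as the SD of change, and the patterns of arm means below, because the article gives no expected interaction.

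**1. Reproduce the plan's figure.** N = 2 × 24.7² × 7.9 / 17² = 33.4, so 34 per arm. With 20 % dropout, 33.4 / 0.8 = 41.7, so 42, and 4 × 42 = 168. The arithmetic is right, and it is a comparison of one arm with one arm.

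**2. Standard errors with 34 completers per arm.**
- Single arm v placebo: 24.7 × √(2/34) = 5.99.
- Margin, 68 v 68: 24.7 × √(2/68) = 4.24.
- Vitamin D × n-3 interaction: 24.7 × √(4/34) = 8.47.

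**3. Difference detectable with 80 % power** (2.80 × standard error): 16.8 units for a single arm v placebo, 11.9 for the margin if effects are additive, and 23.7 for the interaction.

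**4. Power at 17 units** (normal approximation).
- Single arm: 17/5.99 − 1.96 = 0.88, so 81 %.
- Margin: 17/4.24 − 1.96 = 2.05, so 98 %.
- Interaction of 17 units: 17/8.47 − 1.96 = 0.05, so 52 %.

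**5. How often the two verdicts differ.** This was simulated with 400,000 trials per row, t tests on 132 degrees of freedom with pooled variance, and two-sided 5 % for each contrast. The t tests put power up to about one point below step 4. Mean improvements are listed as placebo / D / n-3 / both.

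| Pattern | Margin for D | D alone v placebo | Verdicts differ |
|---|---|---|---|
| 0/17/0/17 (additive) | 98 % | 80 % | 18 % |
| 0/12/0/12 (additive) | 80 % | 51 % | 33 % |
| 0/17/17/17 (no added benefit of both) | 51 % | 80 % | 33 % |
| 0/0/0/17 (benefit only in combination) | 51 % | 5 % | 51 % |
| 0/0/0/0 | 5 % | 5 % | 7 % |

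**6. Sensitivity to the SD.** The article describes the SD as "on a mean SRS and standard deviation of 105 and 24.7 units in untreated children with ASD", which reads as an SD of the score. The SD of change is then 24.7 × √(2(1 − r)), where r is the baseline-to-12-month correlation. It equals 24.7 only at r = 0.5. At an assumed r = 0.7 it is 24.7 × √0.6 = 19.1. Disagreement falls to about 5 % at an additive 17 units and about 24 % at 12 units. It stays near 24 % for 0/17/17/17 and rises above 70 % when only the combination helps.

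**The case against.** The best defence is that coding and post-hoc lists belong in a statistical analysis plan, and that sizing by arm is a legitimate, cautious choice when arm effects or an interaction are of interest. Both are fair. But the article itself states the design, the sizing contrast, the primary model and the follow-up rule, and it does not link them. *Participants* does name a contrast for sizing; the analysis section does not carry it forward as the deciding test.

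A reader might go further and infer that the trial is explicitly tested as four arms, with the Bonferroni rule as proof. The text does not support that. The plural wording and the reference to main effects fit two-factor coding equally well. Adjusted comparisons among the four cells can also follow a significant factorial interaction.

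A reader might also quote larger disagreement, about 41 % at 17 units and 55 % at 12, by setting the margin against a six-pair Bonferroni test after a significant overall test. The plan specifies neither six pairs nor such a gate, so the equal-alpha figures of 18 % and 33 % are the fair ones.

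Finally, the gain from the margin depends on additivity, and the sponsor postulates an interaction. That objection stands. It is a reason to fix the contrast and the interaction term together.

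**Conclusion.** The concern holds as an ambiguity in the stated primary analysis. The sample size is correctly calculated for a single arm against placebo. The analysis section does not say how treatment is coded or which contrast decides each hypothesis, and the only methods it names for the nutrient interaction suit a binary outcome.

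Under the sponsor's inputs and additivity, the choice is worth 98 % against about 80 % power at 17 units, and 11.9 against 16.8 units detectable. Verdicts differ in about 18 % of trials, or about 33 % at 12 units. If 24.7 is a score SD and the correlation is 0.7, these become about 5 % and 24 %. Without additivity either contrast can be the more powerful.

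It would be wrong to conclude that the trial discards half its information: that would require both four-level coding, which is not stated, and additive effects, which are not known. The change should be made, since it is nearly free. The trial was still recruiting when the article was submitted.

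**What to change.** In *Data handling and statistical analysis*:

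- Code vitamin D (yes/no) and n-3 LCPUFA (yes/no) as two factors with their product term, each by time, on the score scale. Keep the outcome as change from baseline to 12 months.
- Name the deciding contrasts before unblinding. For the second hypothesis, use the two factorial main effects, read with the interaction estimate. For the third, use the combination against each supplement and against placebo.
- State how alpha is handled across the two main effects.
- Report all simple effects with confidence intervals whatever the test results.

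In *Participants*, say that 42 per arm refers to a single arm against placebo (about 17 units detectable), and that the margins, with 68 v 68 completers, detect about 12 units with 80 % power if effects are additive.

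**Cost.** Wording only: no extra children, visits or measurements. The downside is that, under strong interaction, each main effect is an average over the other nutrient and must be read with the simple effects. Power for the interaction itself stays modest (52 % for 17 units), so a non-significant product term would not establish additivity.

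### The vitamin D by omega-3 interaction on score outcomes is assigned to logistic regression and Rothman's synergy index, and the stated reading of that index does not hold for effects that add on the score

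*Protocol article*

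**What the plan says.** All points are from the Protocol article.

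- **Outcomes (abstract, Methods/design).** "The primary outcome measures are the change in social-communicative functioning, sensory processing issues and problem behaviours between baseline and 12 months". Table 1 measures these by SRS-2, SPM and ABC-C, all of which are scores.
- **Sample size (Participants).** The calculation uses a 17-unit difference in SRS change and SD 24.7. The term in the denominator "is the difference in SRS total score between groups".
- **Primary model (Data handling and statistical analysis).** The treatment comparison "will be conducted using a generalised linear mixed-models procedure". On the terms of that model, the section then says: "Treatments and time will be included as fixed effects and the interactions between interventions and time will be tested". Post-hoc tests with Bonferroni adjustment follow.
- **Interaction of the two nutrients (same section).** "Logistic regression will be used to test the multiplicative interaction". The second tool named is the synergy index of Rothman, described as one "which would be equal to unity under additivity, and less than unity when suggesting antagonism". It is assigned to the postulated "interaction effect of vitamin D and omega-3 LCPUFAs on core symptoms of ASD".

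The article gives no binary version of a core-symptom outcome: no cut-off, no event and no direction of coding.

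**The concern.** Logistic regression and the synergy index both describe the probability of an event. Here the outcomes are scores, the design assumption is a difference in means, and the primary model can work on the scores directly. Cutting the scores for the interaction alone has two costs.

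First, it discards information in the comparison that already has the least power in a 2 × 2 trial.

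Second, it changes the scale on which additivity is judged. The plan fixes the reading of the index in advance: 1 is additivity and below 1 is antagonism. If two supplements that simply add on the SRS score give a value away from 1, the trial could report synergy or antagonism where neither exists on the scale for which it was designed. The choice of method and the reading of the index are both stated in the article, so this is more than a detail deferred to an analysis plan.

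**Working it through.** **The plan's own figure.** N = 2 × SD² × K / difference² = 2 × 24.7² × 7.9 / 17² = 33.35, so 34 per arm. With 20 % dropout, 33.35 / 0.8 = 41.7, so 42 per arm and 4 × 42 = 168 in total. The stated sizes reproduce. No figure is given for the interaction.

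**Inputs.** SD 24.7 and the 17-unit difference come from Participants; 24.7 is taken as the SD of change, as the plan's formula does. Assumed here: normal scores, no mean change on placebo, equal single-supplement effects of 8.5 or 17 units that add exactly, and response = a fall of at least 17 units.

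**Formula.** S = (R11 − 1) / [(R10 − 1) + (R01 − 1)], where R is the ratio against placebo for both supplements (11) or one (10, 01). Logistic regression gives odds ratios (OR). Response probability = Φ((effect − 17) / 24.7).

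**8.5 units each, 17 together.** Response is 24.6 % (placebo), 36.5 % (either) and 50.0 % (both).
- Event = response: OR10 = 1.77, OR11 = 3.07; S = 2.07 / (2 × 0.77) ≈ **1.35**.
- Event = non-response: OR10 = 0.566, OR11 = 0.326; S = −0.674 / (2 × −0.434) ≈ **0.78**.

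**17 units each, 34 together.** Response is 24.6 %, 50.0 % and 75.4 %.
- Event = response: OR10 = 3.07, OR11 = 3.07² ≈ 9.43; S = 8.43 / (2 × 2.07) ≈ **2.04**.
- Event = non-response: OR10 = 0.326, OR11 = 0.106; S = −0.894 / (2 × −0.674) ≈ **0.66**.

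**Other cut-offs (0 to 34 units), odds-ratio S.**

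| Effect per supplement | Event = response | Event = non-response |
|---|---|---|
| 8.5 units | 1.35 to 1.41 | 0.74 to 0.79 |
| 17 units | 1.94 to 2.38 | 0.63 to 0.67 |

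No cut-off examined gave 1.

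**Risk ratios instead.** S reduces to (p11 − p00) / (p10 + p01 − 2 × p00), which is the same under either coding. It still depends on the cut-off. At 17 units each it is (0.916 − 0.500) / (2 × 0.254) = 0.82 for a cut-off of 0, 1.00 for 17, and 1.29 for 34.

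**Logistic product term.** Recoding the event only inverts it. At 17 units each it is 1.15 (cut-off 0), 1.00 (17) and 0.87 (34) for response, and 0.87, 1.00 and 1.15 for non-response. Its main fault is lost information. In a simulation with 34 per arm, single effects of 8.5 units, a 17-unit interaction and the same cut-off, power was about 51 % for the score contrast and 30 % for the logistic interaction.

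**Stability of S.** The denominator is the sum of the two single-supplement excesses. It nears zero when both are small or when they cancel. In simulation at 34 per arm with 8.5 units each and event = response, it was zero or negative in about 9 % of trials.

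**Contrast on the score.** Combined − vitamin D − omega-3 + placebo is exactly 0 under additive means, with no cut-off or coding. SE = 24.7 × √(4/34) = 8.47; 95 % half-width 1.96 × 8.47 = 16.6; power for a 17-unit interaction Φ(17/8.47 − 1.96) = 52 %; detectable at 80 % power 2.80 × 8.47 = 23.7 units.

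**The case against.** **The index is not the primary analysis.** This stands. The mixed model is primary, and the sample size and treatment comparisons do not depend on the index. A reader might infer that the third hypothesis would be decided by the index. The documents do not support that: under Hypotheses it is worded as the combination being better than either supplement alone or placebo. That is superiority, it is true even when effects merely add, and the mixed-model comparisons can test it.

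**The plan does not say the index comes from odds ratios.** Also true. The preceding sentence names logistic regression, so odds ratios are the natural reading, but the reversal between codings is conditional on them. With risk ratios only the dependence on the cut-off remains.

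**Event and cut-off may be left to an analysis plan.** They may. A pre-defined event would remove the arbitrary coding, but not the mismatch of scale or the fixed reading of the index.

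**The values of S ignore sampling error.** Fair. In simulation at 34 per arm with additive effects of 8.5 units, false synergy under response coding was rare (about 1 %). Under non-response coding, false antagonism was more common: about 15 to 20 %, and 40 to 50 % at 17 units. The risk of a firm false claim is thus largely one-sided.

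**The mixed model may already cover the interaction.** The intervention-by-time wording could be stretched to a vitamin D by omega-3 by time term. The section names no such term, however, and gives the interaction of the nutrients to the other two methods.

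**Conclusion.** The concern holds for the interaction conclusion. For effects exactly additive on the SRS score, an odds-ratio index reads as synergy or antagonism according to how the event is coded (1.35 or 0.78; 2.04 or 0.66). A risk-ratio index is free of the coding problem but moves between 0.82 and 1.29 with the cut-off at 17 units each. The stated rule that 1 means additivity therefore does not carry over to additivity on the score. These sizes rest on SD 24.7 for change, normality, and the assumed single effects and cut-offs; the article gives no single-supplement split and no cut-off.

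Two further inferences should be avoided. The logistic test of multiplicative interaction does not reverse with coding. Nor does the index become unstable merely because one supplement has no effect: the formula shows that both single effects must be small, or must cancel.

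**What to change.** In Data handling and statistical analysis, enter vitamin D and omega-3 as two factors in the planned mixed model. Estimate the interaction as (combined − vitamin D − omega-3 + placebo) in 12-month score change, with a 95 % CI. The primary outcomes are scheduled only at baseline and 12 months, so this is the vitamin D by omega-3 by time term. Zero then means additivity on the scale used to size the trial.

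For the primary outcomes, drop the logistic regression and the synergy index. Alternatively, keep them as exploratory, with the event, cut-off and ratio measure defined before unblinding, and without the fixed reading of the index.

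The cost is wording only: no new data and no change in sample size, and Trial status reports recruitment still under way at submission. The downside is the contrast's limited precision (SE about 8.5 SRS units at 34 per arm, about 52 % power for a 17-unit interaction). The plan should state this, so that a wide interval covering zero is not taken as proof of additivity.
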